### Screening Workflow

Eligible outpatient participants will be invited to participate in the study during routine clinic visits. After providing written informed consent, participants will undergo color fundus photography as part of the screening procedure.

For participants with fundus images, screening findings will be reviewed by the general medicine physicians. Participants without suspected retinal abnormalities will be advised to undergo routine follow-up according to standard clinical practice, whereas participants with suspected retinal abnormalities will be referred to ophthalmology for confirmatory evaluation. Ophthalmologic diagnoses will be established by ophthalmologists, and these will serve as the gold standard for determining true disease status and for calculating the detection rate and positive predictive value (PPV) of DR and AMD screening. Referral completion and diagnostic outcomes will be recorded, including cases in which referred participants did not attend the ophthalmology visit. Outcomes will be classified as confirmed or nonconfirmed retinal disease based on ophthalmologic assessment.

### AI Platform Functionality

AI-assisted retinal screening will be operationalized through the AI Imaging Management, Integration, and Governance System (AIMIGS), a centralized platform designed to govern, integrate, and deploy medical imaging–based AI models within routine clinical workflows (Figure 2). Within this trial, AIMIGS automatically routes eligible fundus photographs from the hospital Picture Archiving and Communication System (PACS) to the designated AI screening models (VeriSee DR and VeriSee AMD) according to predefined rules based on imaging modality, clinical order information, and participant allocation. AI-generated outputs, including image quality assessment, disease suspicion, and screening parameters, will be collected and returned to the AI PACS server and report information system, where they will be made available to treating physicians during clinical encounters. Clinicians are provided with AI-assisted outputs integrated into the clinical workflow. These include referral recommendations (positive or negative), disease severity grading for DR and AMD, image quality assessment, and lesion-level annotations where applicable. The AI results are presented through the electronic health record (EHR) system to support clinical decision-making. The AI system evaluates fundus images based on predefined technical criteria (eg, clarity, illumination, and visibility of key retinal structures), and images not meeting these criteria will be flagged as insufficient quality (Figure 3). Physicians may also independently identify images as inadequate for clinical interpretation. In such cases, repeat imaging will be performed. AIMIGS incorporates a rule engine module that enables automated and protocol-compliant random assignments.

**Figure 2. F2:**
[figure not shown]
The randomization module within the AI Imaging Management, Integration, and Governance System (AIMIGS) rule engine. AI: artificial intelligence; PACS: Picture Archiving and Communication System; RIS: Report Information System.

**Figure 3. F3:**
[figure not shown]
Artificial intelligence–assisted screening output indicating insufficient image quality. (A) Fundus image of diabetic retinopathy. (B) Fundus image of aAge-related Macular Degenemacular degenerraration.

When the input fundus image does not meet predefined quality criteria, the AI system classifies the image as inadequate for clinical interpretation and generates a notification indicating that the image quality is insufficient for analysis. In such cases, repeat image acquisition is required.

AIMIGS includes 3 primary storage components for managing AI model information, rule information, and AI result data, along with 6 functional modules: AI model governance, rule engine, job dispatcher, AI result data collector, monitoring dashboard, and Report Information System integrator. The randomization module is implemented as a core function within the rule engine. Following fundus photography acquisition, the original retinal images are transmitted to and stored in the PACS server. The job dispatcher then executes participant randomization according to the predefined rules in the rule engine and, based on the assigned study arm, determines whether DICOM images should be retrieved from the PACS server and forwarded to the VeriSee model for AI analysis or withheld from AI processing. AI-generated outputs are subsequently transmitted to the AI PACS server, and the AI-generated reports can be further integrated into the EHR as part of the clinical documentation.

In addition to supporting clinical trial randomization, AIMIGS serves as a comprehensive AI image management platform. Key modules include AI model governance for registration and lifecycle tracking; rule engine and task assignment for directing DICOM images to the appropriate AI models; results collection for storing images, reports, and diagnostic parameters; a monitoring dashboard to oversee performance and workflow; and an image-report integration module that facilitates report drafting, prioritization, and communication with the Radiology Information System or PACS.

### Randomization

Participants will be randomized at the individual level in a 1:1 ratio to either the AI-assisted screening group or the conventional physician-based screening group. Randomization is performed on a per-participant basis, and sample size estimation will be based on this process. DR and AMD are managed within a single unified cohort. DR and AMD can be diagnosed in the same patient, while DR and AMD are treated as separate disease-specific outcomes, and analyses will be conducted independently for each condition based on predefined eligibility criteria. Participants eligible for both conditions may contribute to both analyses.

In the conventional physician-based screening arm, fundus photographs will be interpreted by physicians without the use of any AI assistance. Physicians will review the images independently based on their clinical judgment. All physicians involved in image interpretation will receive standardized training in fundus photograph assessment prior to study initiation. In addition, a standardized reading guide will be provided to ensure consistency in image interpretation across the control group.

Randomization will be conducted using a computerized randomization module embedded within the rule engine of AIMIGS. After enrollment, each participant will be assigned a unique study ID, and allocation will be automatically generated by AIMIGS. Once the assignment is generated, the system automatically allocates each participant to the designated study arm and triggers the corresponding imaging procedures according to the predefined workflow.

### Intervention

The intervention consists of an AI-assisted retinal screening strategy using validated screening software (VeriSee DR and VeriSee AMD) for DR and AMD in routine outpatient care. The comparator consists of a conventional physician-based retinal screening strategy without AI assistance.

Participants assigned to the AI-assisted screening group will undergo color fundus photography as part of usual clinical care and will be screened using the AI-assisted approach. Treating physicians will be provided with AI-generated screening outputs, including image quality assessment, disease suspicion, and referral recommendations, in conjunction with fundus images during the clinical encounter. On the basis of this information, physicians will determine whether referral for confirmatory ophthalmologic evaluation is indicated. Participants assigned to the conventional screening group will undergo color fundus photography alone. Fundus images will be reviewed by treating physicians without AI assistance, and referral decisions will be made based solely on physicians’ independent clinical judgment (Figure 4).

**Figure 4. F4:**

Workflow of artificial intelligence (AI)–assisted fundus screening integrated with Picture Archiving and Communication System (PACS) and electronic health record (EHR).

The clinical workflow begins with the physician issuing an AI-assisted fundus photography order, followed by fundus photography acquisition and image upload to the PACS. The AI system then retrieves the images and triggers randomization via the AIMIGS system. In the experimental group, images undergo AI analysis, and the results are uploaded back to AI PACS. In the control arm, images are not analyzed by AI. Finally, physicians review the results in the EHR.

When a fundus image is considered insufficient for clinical interpretation, trained health care personnel will immediately reacquire the image on-site and reassess its quality. This process will not require any additional clinic visits or rescheduling. In both the AI-assisted and conventional screening arms, retinal imaging, image interpretation, and referral decisions are performed identically, ensuring that both groups follow the same care pathway at the same clinical time point. Both study arms follow an identical workflow. The only difference between groups is that the AI-assisted arm provides an additional AI-generated output to support physician decision-making, whereas the control arm relies solely on physician interpretation without AI assistance.

### Referral After a Positive Test

The examination will be repeated for images that are of insufficient quality for clinical interpretation. Across both groups, ophthalmology referral will be provided for participants with DR of stages 2 to 4 or AMD of stages 3 to 4, whereas participants not meeting these severity thresholds will be advised to undergo regular annual follow-up examinations. Confirmatory diagnosis of DR and AMD will follow the Early Treatment Diabetic Retinopathy Study [16], AREDS scales [23], and Beckman Initiative Classification [23] (Textbox 1). At 8 weeks after screening, referral completion and diagnostic outcomes will be assessed through review of electronic medical records, hospital visit records, and, when necessary, telephone follow-up.

Textbox 1.Confirmatory diagnosis of diabetic retinopathy (DR) and age-related macular degeneration (AMD).Diabetic retinopathyAccording to the Early Treatment Diabetic Retinopathy Study severity scale [24], primarily diagnosed through fundus photography and indirect ophthalmoscopy to identify typical features such as microaneurysms, retinal hemorrhages, hard exudates, and cotton-wool spots (soft exudates).Fluorescein angiography is generally not used as a primary diagnostic tool; however, it may be used in the evaluation of macular ischemia, edema, or neovascularization to inform treatment strategies. It facilitates the verification of the location and extent of lesions.The severity of DR is categorized into 5 stages: no diabetic retinopathy (no DR, stage 0), mild nonproliferative diabetic retinopathy (NPDR; stage 1), moderate NPDR (stage 2), severe NPDR (stage 3), and proliferative diabetic retinopathy (PDR; stage 4).Age-related macular degeneration:According to the Age-Related Eye Disease Study severity scale [25], fundus photography and indirect ophthalmoscopy are primarily used to identify the location, size, and number of drusen.On the basis of the Beckman Initiative Classification [23], AMD is classified into 4 severity levels based on drusen size and pigmentary abnormalities: no AMD (stage 1), early AMD (stage 2), intermediate AMD (stage 3), and advanced AMD (stage 4).When necessary, fluorescein angiography and optical coherence tomography are used to detect the choroidal neovascularization associated with AMD, the presence of macular edema, and retinal pigment epithelium abnormalities.

After completing the fundus photography, participants will be invited to complete a satisfaction survey regarding the screening method. Additionally, physicians participating in the study will be required to complete a satisfaction survey at the end of the trial, reflecting their experiences using the AI-assisted screening tool.

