#### Exploratory Outcomes

Exploratory outcomes include (1) screening participation rate, assessed by the number of participants and nonparticipants; (2) referral completion rate, defined as the proportion of referred participants who completed ophthalmologic confirmatory evaluation within the prespecified 2-month follow-up period; (3) patient satisfaction, evaluated using a posttrial survey; (4) whether AI-assisted screening reduces clinical decision-making time and physician workload, evaluated using a posttrial survey; (5) time to diagnosis of DR or AMD; and (6) visual loss as the long-term outcome.

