
### Conclusions

This study aims to evaluate the clinical effectiveness and feasibility of incorporating AI-assisted retinal screening tools into routine practice. By comparing AI-assisted and traditional screening methods, the trial will generate evidence on whether these tools improve early detection, enhance referral efficiency, and increase patient and physician satisfaction. The results are expected to guide the broader adoption of AI technologies in ophthalmic care, leading to more accessible, timely, and precision-oriented eye health services.

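### Patient-survey timing is stated in two ways, one of which allows a survey before the arms differ, and the physician survey as described has no control-arm counterpart to show a reduction in decision time or workload

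*Protocol article*

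**What the plan says.** **Patient survey.** Two places describe it.

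- Methods, Referral After a Positive Test: "After completing the fundus photography, participants will be invited to complete a satisfaction survey regarding the screening method".
- Exploratory Outcomes, item 3: "patient satisfaction, evaluated using a posttrial survey".

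**Physician survey.** Referral After a Positive Test says that "physicians participating in the study will be required to complete a satisfaction survey at the end of the trial", with the content described as "reflecting their experiences using the AI-assisted screening tool". Exploratory Outcomes, item 4, sets the question this has to answer: "whether AI-assisted screening reduces clinical decision-making time and physician workload, evaluated using a posttrial survey". No other physician instrument is described.

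**Where the arms separate.** The Figure 4 workflow in Intervention has the photograph taken and uploaded first, and then: "The AI system then retrieves the images and triggers randomization via the AIMIGS system". The platform description under AI Platform Functionality gives the same order. Intervention adds that the AI output offered to the physician is the sole difference between the arms.

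**What the data are for.** Principal Results gives a modest purpose: feasibility, acceptability and perceived usefulness. Conclusions goes further and says the trial will give evidence on whether the tools "improve early detection, enhance referral efficiency, and increase patient and physician satisfaction". The Results section states, as a property of the tools, that they lower physicians' workload.

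**The concern.** A randomized comparison of satisfaction is informative only if the respondent has experienced what differs between the arms. Here the difference arises when the physician reads the image with or without the AI output, which is after photography. If sites take the Methods wording at face value and hand out the form once the photograph is done, most of what participants rate will be the same in both arms. The comparison will then tend towards no difference for reasons unrelated to AI. If other sites follow the outcome wording and ask at the end, responses collected at different stages of care will be pooled.

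For physicians the difficulty is one of contrast. Outcome 4 is worded as an effect of AI relative to usual reading. A single retrospective survey about the AI tool, answered by physicians who know when AI was used and who are not themselves randomized, supplies one side of that comparison only.

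At stake is whether two exploratory questions, one of which also appears in the Conclusions, can be answered with the instruments named.

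**Working it through.** No figure in the plan bears on this point, so the check sets the passages side by side.

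**Step 1. Order of events for the participant.**

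1. Consent.
2. Fundus photography and upload (Screening Workflow; Figure 4 workflow).
3. Randomization by the AIMIGS rule engine, triggered after the image is stored (AI Platform Functionality; Figure 4 workflow).
4. AI analysis in one arm, none in the other.
5. Physician review in the electronic record and decision on referral.
6. Result communicated; referral outcome checked at 8 weeks.

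The section headed Randomization is less clear on order. It has allocation generated after enrollment, with the assignment then setting off the imaging procedures. The two workflow descriptions are explicit that the photograph comes first, and I follow them here.

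**Step 2. Place the patient survey in that order.** The Methods sentence fixes only that the survey comes after step 2. Any time from just after step 2 onwards satisfies it. The outcome wording places the survey after the trial, which would be after step 6. The two overlap only if the survey is held late, and nothing in the text says so.

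**Step 3. What a respondent has experienced at each point.**

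| Survey given | Arm-specific experience so far |
|---|---|
| Just after photography | Little: possibly a repeat photograph prompted by an AI quality flag |
| After the result is communicated | The physician's reading with or without AI, and the return of the result |
| After the trial | The same, plus any referral |

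The second and third rows allow a comparison by randomized arm. The first is largely uninformative. Principal Results reinforces this: it puts the contrast visible to patients in how results come back, promptly with AI and at follow-up appointments in the control group. That sits awkwardly with Intervention, which says both arms follow the same pathway at the same clinical time point. Tying the survey to an event, the communication of the result, rather than to a date covers both descriptions.

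**Step 4. Physician question against physician instrument.**

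| | Outcome 4 asks for | Survey as described gives |
|---|---|---|
| Quantity | Decision time and workload | Experience with the AI tool |
| Contrast | Reduction relative to usual reading | None stated |
| Randomized unit | Participant or encounter | Physician, not randomized |
| Blinding | Not applicable | Unblinded (Study Design) |
| Timing | Per reading | Once, at the end, by recall |

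No baseline, control-arm reading survey or per-encounter timing is described. The instrument fits the purpose given in Principal Results. It does not fit the word reduces in outcome 4.

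**Step 5. Extent.** Exploratory Outcomes lists six items; items 3 and 4 are affected. Detection rate, PPV and the cost-effectiveness analysis as described do not draw on either survey.

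**The case against.** The strongest reply is that this is wording in exploratory outcomes. Several parts of it stand.

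- The Methods sentence sets an earliest time, not a fixed one, and the outcome list says the survey is held after the trial. A reader might infer that patient satisfaction is surveyed at the camera and that the comparison is null by construction. The text does not support that: a survey after the result could be compared by arm.
- Even just after photography the arms need not be identical. The AI arm can produce a quality flag and an immediate on-site repeat, so an expected difference of exactly zero cannot be claimed.
- A reader might take the Conclusions as a promise that satisfaction will rise. They say the trial will examine whether it does.
- A reader might assume that decision time could simply be exported from the electronic systems for every randomized participant. The article does not say that those systems log usable times. Data Security lists eligibility, assignments, interpretations and AI outputs as recorded in REDCap, and does not list times.
- The questionnaire is not shown. It may ask physicians to compare assisted with unassisted reading, and that level of detail is often left to a fuller document. That the same physicians read for both arms is likely, but not stated.

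What does not fall away is that the article itself fixes two unreconciled times for the patient survey. It also names an instrument for outcome 4 whose described content covers one arm's way of reading only. Those are statements in the document, not omissions from it.

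**Conclusion.** The point holds in two limited parts.

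**Patients.** The two descriptions of survey timing conflict, and one of them permits a survey before the participant has met the difference between arms. Done then, the survey would be largely uninformative about AI. It does not follow that the trial cannot assess patient satisfaction; that depends on which timing is used. This rests on the sequence in the two workflow descriptions, photography before randomization.

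**Physicians.** As described, the end-of-trial survey can show perceived usefulness but not a reduction in decision time or workload relative to control. This assumes that the survey's content is what the article says it is.

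The size is modest: two of six exploratory outcomes, with no effect on the primary outcomes. Correction is still worthwhile because outcome 4 is worded as an effect of AI, the Conclusions say the trial will address satisfaction, and the Results section already states the workload benefit as fact.

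**What to change.** 1. **Patient survey.** In Referral After a Positive Test and in Exploratory Outcomes, state one and the same time: after the screening result has been communicated, tied to the same event in both arms. State that responses are compared by randomized arm. Cost: a change of wording and timing, and possibly a lower response than when people are asked on the spot.
2. **Physician survey.** Have physicians rate AI-assisted and unassisted reading separately. Cost: form wording. The answers remain unblinded recall and should be described as such.
3. **Decision time.** If the systems already log times, which the article does not state, compare the interval from image availability to recorded interpretation by randomized arm. Cost: a data export; the interval will include idle time in both arms. If times are not logged, reword outcome 4 as physicians' perceptions of decision time and workload.
4. **Claims.** Bring the workload statement in Results and the satisfaction statement in Conclusions into line with what is measured. Cost: wording only.

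The abstract places randomization after the pilot phase, so the forms and their timing can be settled before randomized participants are surveyed, provided the change is made before that phase starts.

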### Performance of AI-Assisted Ophthalmic Screening Tools

Both screening tools are based on the convolutional neural networks for image segmentation and classification of disease severities. Both tools received approval from the Taiwan Food and Drug Administration in 2020 (MOHW-MD-No.006966 and MOHW-MD-No.007652), with both classified as “Class II medical devices.” Once installed on a compatible computer, the software will automatically assess image quality and generate preliminary diagnostic outputs, which are immediately shared with attending physicians to support clinical decision-making. VeriSee DR uses deep learning algorithms to identify key DR features, including microaneurysms, hemorrhages, soft exudates, and hard exudates. The tool also offers referral recommendations, categorized as routine follow-up or ophthalmology referral.

The diagnostic accuracies of VeriSee DR and VeriSee AMD have been previously reported [13,26]. For DR, prior validation studies reported a sensitivity of 92.2% and a specificity of 89.5% [13]. For AMD, the results were 90% and 92.4%, respectively [26]. Figure 5 illustrates the AI-assisted screening interfaces for DR and AMD. For DR, the interface displays image quality assessment and AI-assessed severity staging with lesion-level annotations, whereas for AMD, the interface provides an AI-generated referral recommendation.

